| Erlotinib                  | To be taken whole half hour before breakfast                                                                                                                                                     | Dose as appropriate for assigned dose level | Oral         | Daily                                                                                                                                |                     |

In cases where the patient's BSA > or equal to 2.0, oral Navelbine dose should not exceed twice the dose/m^2 (e.g. 120 mg for 60 mg/m^2, and 160 mg for 80 mg/m^2) per week. In cases where the BSA < or equal to 1.4, these patients will not be recruited into the metronomic arm – this is for patient safety to avoid excessive dose.

The standard “3+3” rule will be employed for dose escalation. Three patients will be accrued at the starting dose levels. If no dose limiting toxicities greater than grade 2 were observed, 3 patients would be entered at the next dose level. If, at any dose level, one of the first 3 patients experiences a DLT, 3 additional patients will be entered at that dose level. If 2 out of 6 patients experience dose-limiting toxicities at this dose level, dose escalation will cease.

The maximally tolerated dose (MTD) will be defined as one dose level below that at which 2 or more patients experienced DLT. If DLT is observed at initial level of either schedule, an additional 3 patients will be accrued at the –1 level. If DLT is observed at this level, the trial will be terminated.

A patient who experiences any DLT will be allowed to continue treatment with a one dose level reduction if the toxicity resolves within 14 days. If this patient experiences a DLT at the lowered dose level, study treatment will be stopped for this patient.

No intra-patient dose escalation will be allowed. Re-entry of a patient accrued at a lower dose into a higher dose cohort will not be allowed. Accrual rate is expected to be 3-4 patients per month. Dose escalation will proceed within each cohort according to the following schedule.

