| Number of Patients with DLT at a Given Dose Level                             | Escalation Decision Rule                                                                                                                                                                                                                                                                                                                                                                                                                                           |
|-------------------------------------------------------------------------------|--------------------------------------------------------------------------------------------------------------------------------------------------------------------------------------------------------------------------------------------------------------------------------------------------------------------------------------------------------------------------------------------------------------------------------------------------------------------|
| 0 out of 3                                                                    | Enter 3 patients at the next dose level.                                                                                                                                                                                                                                                                                                                                                                                                                           |
| $\geq 2$                                                                      | Dose escalation will be stopped. This dose level will be declared the maximally administered dose (highest dose administered). Three (3) additional patients will be entered at the next lowest dose level if only 3 patients were treated previously at that dose.                                                                                                                                                                                                |

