| 1 out of 3                                                                    | Enter at least 3 more patients at this dose level. 
 
• If 0 of these 3 patients experience DLT, proceed to the next dose level.
 
• If 1 or more of this group suffer DLT, then dose escalation is stopped, and this dose is declared the maximally administered dose. Three (3) additional patients will be entered at the next lowest dose level if only 3 patients were treated previously at that dose.
 
 |
| $\leq 1$ out of 6 at highest dose level below the maximally administered dose | This is generally the recommended phase 2 dose. At least 6 patients must be entered at the recommended phase 2 dose.                                                                                                                                                                                                                                                                                                                                               |

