## **13.1 Analysis**

- The primary aim of this study is to determine the dose limiting toxicities of oral vinorelbine combined with erlotinib and the maximal tolerated dose (MTD) of this drug combination in patients with non-small cell lung cancer. The toxicity profile will be graded as described above and reported with the corresponding dose level.
- The MTD will be dose at which less than 2 DLTs occur. Steady state plasma drug

concentrations, area under the curve values, volume of distribution and clearance of oral vinorelbine and erlotinib in each patient will be calculated and correlated with dose. These quantities will be summarized for all patients.

- Response rates (Complete response, partial response, stable disease) to study treatment will be described based on RECIST criteria and summarized by dose. Overall survival will be measured from registration to death and analyzed by the Kaplan-Meier method.
- Exploratory analysis of known functional SNPs in the transporter genes will be described in relation to dose and response. An exploratory analysis of the changes on CEC/CEP assessment of angiogenesis in each group would be performed.

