### 13.2 Sample size considerations:

As this is a phase 1 study, no formal sample size calculation is possible. The number of patients accrued will depend on the DLT reached on each arm of the study. Between 3-6 patients will be observed on each dose levels and an expanded cohort of 6 patients will be observed on the MTD. The anticipated accrual to this study is between 12 (if there are at least 2 DLT at dose level 1 and DLT at level -1) to 78 patients (if dose level 5 is reached and the cohort receiving erlotinib 150 mg is included).

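### Section 5.1 stops at level -1 on an uncounted DLT, which contradicts the protocol's own 3+3 rule when 1 of the first 3 patients has a DLT

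*Protocol*

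**What the plan says.** The Protocol, section 5.1 (Agent Administration), sends 3 patients to level -1 if DLT is observed at the initial level of either schedule, and then states: "If DLT is observed at this level, the trial will be terminated". Neither sentence gives a number of DLTs.

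Other statements bear on the same situation:

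- Section 5.1, 3+3 text: if, "at any dose level, one of the first 3 patients experiences a DLT, 3 additional patients will be entered at that dose level". Escalation ceases at 2 of 6.
- Section 5.1, MTD definition: the MTD "will be defined as one dose level below that at which 2 or more patients experienced DLT".
- Section 5.1, decision table: at most 1 "out of 6 at highest dose level below the maximally administered dose" is generally the recommended phase 2 dose, and "At least 6 patients must be entered at the recommended phase 2 dose".
- Section 13.1: "The MTD will be dose at which less than 2 DLTs occur".
- Section 13.2: the minimum accrual of 12 applies "if there are at least 2 DLT at dose level 1 and DLT at level -1".

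Section 1.1 lists the MTD of the conventional schedule and the MTD of the metronomic schedule as separate primary objectives.

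**The concern.** If 2 or more patients have a DLT at level 1 of a schedule, level -1 is the only remaining candidate for that schedule's MTD. The stopping sentence then decides whether the primary objective is met for that schedule. Suppose 1 of the first 3 patients at level -1 has a DLT. The 3+3 rule enters 3 more patients, and if none of them has a DLT, 1 of 6 qualifies under both the decision table and section 13.1. The stopping sentence instead ends the trial at the first DLT. Two teams following the same document could declare an MTD or close with none.

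The word for what closes is also imprecise. The sentence before refers to either schedule, whereas the stop refers to the trial as a whole. Section 5.1 says that the other schedule continues when one has reached its MTD, but it does not cover failure at level -1.

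**Working it through.** **The plan's own figure.** Minimum accrual: 2 schedules × (3 at level 1 + 3 at level -1) = 12, which matches section 13.2. This needs both schedules to run both levels. If the first DLT at level -1 closed the whole trial, accrual could end at about 3 (conventional, level 1) + 3 (metronomic, level 1) + 3 (conventional, level -1) = 9. The stated 12 therefore points to closure by schedule. It does not settle the DLT count: any DLT in 3 and 2 or more DLTs in 3 both give 3 patients at level -1.

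**What the rules do at level -1**

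| Result at level -1 | Stopping sentence, read literally | 3+3 text, table and 13.1 |
|---|---|---|
| 2 or more of 3 | stop | stop |
| 1 of 3 | stop | enter 3 more |
| 1 of 3, then 0 of 3 | already stopped | 1 of 6, acceptable |
| 0 of 3, then 1 of 3 | unclear whether the stop still applies | 1 of 6, acceptable |

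The direct conflict is in the second and third rows. The fourth conflicts only if the stop carries over to the second 3 patients.

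**Size, given that level -1 is reached.** The protocol states no DLT rates, so p, the true rate at level -1, is an assumption.

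- Literal stop, any DLT in 3: 1 − (1−p)³
- 3+3 stop: P(2 or more of 3) + 3p(1−p)² × [1 − (1−p)³]
- Clear conflict, 1 of 3 then 0 of 3: 3p(1−p)² × (1−p)³ = 3p(1−p)⁵
- Exactly 1 of 6, either order: 6p(1−p)⁵

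| p | Literal stop | 3+3 stop | Clear conflict | Exactly 1 of 6 |
|---|---|---|---|---|
| 5% | 14.3% | 2.7% | 11.6% | 23.2% |
| 10% | 27.1% | 9.4% | 17.7% | 35.4% |
| 20% | 48.8% | 29.1% | 19.7% | 39.3% |

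As a check, literal stop minus 3+3 stop equals the clear conflict in each row; for example, 27.1% − 9.4% = 17.7%.

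**Size per schedule, not conditional on reaching level -1.** With true rate q at level 1, the probability of leaving level 1 downwards on the first pass under 3+3 is 1 − [(1−q)³ + 3q(1−q)⁵]. For q = 10% this is 1 − (0.729 + 0.177) = 0.094. Multiplying by the columns above:

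| Level 1 / level -1 rates | Level -1 reached | Exactly 1 of 6 | Clear conflict |
|---|---|---|---|
| 10% / 5% | 9.4% | 0.094 × 0.232 = 2.2% | 1.1% |
| 15% / 5% | 18.6% | 0.186 × 0.232 = 4.3% | 2.2% |
| 20% / 10% | 29.1% | 0.291 × 0.354 = 10.3% | 5.2% |
| 30% / 20% | 50.6% | 0.506 × 0.393 = 19.9% | 9.9% |

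**The case against.** The strongest defence is that the sentence is a deliberate, stricter rule for the fallback dose. The two places that specifically address a DLT at level -1, sections 5.1 and 13.2, agree, and section 13.2 counts DLTs for level 1 but not for level -1. A zero-tolerance stop there is a legitimate choice: 30 mg/m² is half the labelled 60 mg/m² starting dose, and erlotinib 100 mg is below the 150 mg NSCLC dose. The second defence is the opposite: the protocol sometimes uses DLT as shorthand for the dose-limiting level having been reached, as in the accrual description in section 5.1, and then 2 or more is meant.

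Both readings are possible. They give opposite outcomes for 1 of 3, no sentence chooses between them, and nothing says that the stop overrides a rule stated for any dose level. So neither removes the defect.

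Other parts of the defence stand:

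- The direct contradiction is with the expansion rule. The table row is hedged as what generally applies, and section 13.1 is a one-line definition that does not mention level -1. These two are inconsistent with the stop rather than separate direct contradictions.
- The sentence that opens level -1 is also uncounted, and a reader might infer a second contradiction. The table and section 13.2 already resolve it as 2 or more at level 1.
- A reader might infer that a DLT at level -1 in one schedule is meant to close both, or that the question is open. The 12-patient minimum and the separate MTD objectives imply closure by schedule, so what remains is an imprecise word.
- Level -1 may rarely be reached. Section 2.3 reports single-agent metronomic dosing as tolerated up to 180 mg per week, with DLTs in weeks 9 and 14, outside this trial's first-cycle DLT window. Rates for the combination are unknown. This is why a 10% / 5% scenario is included.

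**Conclusion.** The stopping sentence is wrong as written, with minor to moderate severity. It conflicts directly with the 3+3 expansion rule in the same section and is inconsistent with the decision table and section 13.1; section 13.2 repeats the missing count.

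Given that level -1 is reached, the clear conflict has probability 12%, 18% or 20% at assumed true rates of 5%, 10% or 20%. The higher figures of 23%, 35% and 39% hold only if the stop also applies to the second 3 patients, which the text does not say. Per schedule, without conditioning, exactly 1 of 6 occurs in about 2% to 20% over the scenarios shown, and the clear path in half of that. All of these rest on assumed rates and on the first pass through level 1.

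A reader might infer a safety problem. The documents do not support that, because the literal rule errs towards stopping. What is at stake is consistent conduct, and whether a schedule closes without an MTD after a result that the protocol elsewhere accepts.

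**What to change.** Replace the two sentences in section 5.1 with:

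> If 2 or more patients have a DLT at level 1 of a schedule, 3 patients enter level -1 of that schedule, expanded to 6 if 0 or 1 of the 3 has a DLT. If 2 or more have a DLT at level -1, that schedule closes without an MTD and the other continues; if at most 1 of 6 does, level -1 is the MTD.

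In section 13.2, change the condition for the minimum so that it requires at least 2 DLTs at level 1 and at least 2 at level -1.

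If a stricter stop at level -1 is intended, state its count, whether it also covers the second 3 patients, and that it overrides the table. If closure of both schedules is intended, say so and recheck the minimum of 12.

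The cost is a wording amendment: two sentences and one phrase, with no new procedures. Level -1 may take 6 patients per schedule instead of 3, which the table already requires for a recommended dose and section 13.2 for the MTD. The minimum of 12 is unchanged under the replacement text.

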### **Dose Modifications**

In patients who develop an acute onset of new or progressive pulmonary symptoms, such as dyspnea, cough or fever, treatment with TARCEVA should be interrupted pending diagnostic evaluation. If ILD is diagnosed, TARCEVA should be discontinued and appropriate treatment instituted as necessary.

Diarrhea can usually be managed with loperamide. Patients with severe diarrhea who are unresponsive to loperamide or who become dehydrated may require dose reduction or temporary interruption of therapy. Patients with severe skin reactions may also require dose reduction or temporary interruption of therapy.

When dose reduction is necessary, the TARCEVA dose should be reduced in 50 mg decrements. In patients who are being concomitantly treated with a strong CYP3A4 inhibitor such as, but not limited to, atazanavir, clarithromycin, indinavir, itraconazole, ketoconazole, nefazodone, nelfinavir, ritonavir, saquinavir, telithromycin, troleandomycin (TAO), or voriconazole, a dose reduction should be considered should severe adverse reactions occur.

Pre-treatment with the CYP3A4 inducer rifampicin decreased erlotinib AUC by about 2/3. Alternate treatments lacking CYP3A4 inducing activity should be considered. If an alternative treatment is unavailable, a TARCEVA dose greater than 150 mg should be considered. If the TARCEVA dose is adjusted upward, the dose will need to be reduced upon discontinuation of rifampicin or other inducers. Other CYP3A4 inducers include, but are not limited to rifabutin, rifapentine, phenytoin, carbamazepine, phenobarbital and St. John's Wort. These too should be avoided if possible.

Erlotinib is eliminated by hepatic metabolism and biliary excretion. Therefore, caution should be used when administering TARCEVA to patients with hepatic impairment. Dose reduction or interruption of TARCEVA should be considered should severe adverse reactions occur.

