### **Warnings**

#### **Pulmonary Toxicity**

There have been infrequent reports of serious Interstitial Lung Disease (ILD)-like events, including fatalities, in patients receiving TARCEVA for treatment of NSCLC, pancreatic cancer or other advanced solid tumors. In the randomized single-agent NSCLC study, the incidence of ILD-like events (0.8%) was the same in both the placebo and TARCEVA groups. In the pancreatic cancer study - in combination with gemcitabine, the incidence of ILD-like events was 2.5% in the TARCEVA plus gemcitabine group vs. 0.4% in the placebo plus gemcitabine group.

The overall incidence of ILD-like events in approximately 4900 TARCEVA-treated patients from all studies (including uncontrolled studies and studies with concurrent chemotherapy) was approximately 0.7%. Reported diagnoses in patients suspected of having ILD-like events included pneumonitis, radiation pneumonitis, hypersensitivity pneumonitis, interstitial pneumonia, interstitial lung disease, obliterative bronchiolitis, pulmonary fibrosis, Acute Respiratory Distress Syndrome and lung infiltration. Symptoms started from 5 days to more than 9 months (median 39 days) after initiating TARCEVA therapy. In the lung cancer trials most of the cases were associated with confounding or contributing factors such as concomitant/prior chemotherapy, prior radiotherapy, pre-existing parenchymal lung disease, metastatic lung disease, or pulmonary infections.

In the event of an acute onset of new or progressive, unexplained pulmonary symptoms such as dyspnea, cough, and fever, TARCEVA therapy should be interrupted pending diagnostic evaluation. If ILD is diagnosed, TARCEVA should be discontinued and appropriate treatment instituted as needed

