Reported adverse events and potential risks for Oral Vinorelbine and Erlotinib are described in Section 5.2. Appropriate dose modifications for Oral Vinorelbine and Erlotinib are described in Section 6. No investigational or commercial agents or therapies other than those described below may be administered with the intent to treat the patient's malignancy.

| REGIMEN DESCRIPTION |                                                                                                                                                                                                  |                                             |              |                                                                                                                                      |                     |
|----------------------------|--------------------------------------------------------------------------------------------------------------------------------------------------------------------------------------------------|---------------------------------------------|--------------|--------------------------------------------------------------------------------------------------------------------------------------|---------------------|
| Agent               | Premedications; Precautions                                                                                                                                                               | Dose                                 | Route | Schedule                                                                                                                      | Cycle Length |
| Vinorelbine                | Both erlotinib and vinorelbine will be given after prophylactic administration of antiemetics (preferably 5-HT 3 antagonist) on Day 1 (except for Cycle 1) and on Day 8 of each cycle | Dose as appropriate for assigned dose level | Oral         | Conventional Schedule: Day 1 and 8 of each cycle
Metronomic Schedule: D1,3,5 every 7 days for 3 weeks of each cycle | 21 days (3 wks)     |

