### 5.2 Definition of Dose-Limiting Toxicity

All toxicities will be graded according to the National Cancer Institute Common Toxicity Criteria (NCI CTC version 3). In particular, the following toxicities which tend to be more common with vinorelbine use will be recorded in detail: constipation, haematologic toxicities (neutropenia, thrombocytopenia, anemia), neutropenic infections, infections including pneumonia, urinary tract infection, bacteremia, hepatobiliary sepsis; pneumonitis; ileus; hepatitis; fatigue, weight loss, nausea and vomiting.

Hematological Dose Limiting Toxicity (DLT) is defined as follows: grade 4 neutropenia of >7 days duration, neutropenic fever, grade 4 anemia or grade 3-4 thrombocytopenia that occurs during the first cycle of treatment.

Non-hematologic DLT is defined as any grade 3 or grade 4 non-hematologic toxicity that occurs during the first cycle of treatment.

Any toxicity causing a total of 14 days delay will also be considered dose limiting. Toxicities will be classified as related to the study drug unless they were attributable to either underlying tumour progression, concurrent medical condition or a concomitant medication. Any unusual toxicities must be reported to the Principal Investigator

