## **8.2 Erlotinib**

The 100 mg and 150 mg strengths are supplied as white film-coated tablets for daily oral administration.

TARCEVA (erlotinib) Tablets, 100 mg: Round, biconvex face and straight sides, white film-coated, printed in gray with "T" and "100" on one side and plain on the other side. Supplied in bottles of 30 tablets (NDC 50242-063-01).

TARCEVA (erlotinib) Tablets, 150 mg: Round, biconvex face and straight sides, white film-coated, printed in maroon with "T" and "150" on one side and plain on the other side. Supplied in bottles of 30 tablets (NDC 50242-064-01).

Store at 25°C (77°F); excursions permitted to 15°-30°C (59°-86°F).

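### The Section 5.1 rule for continuing after a DLT does not say which drug is stepped down, leaves erlotinib at 100 mg across vinorelbine levels -1 to 5, and for ILD contradicts the protocol's own Section 2

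*Protocol*

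**What the plan says.** - **Section 5.1, continuing after a DLT:** "A patient who experiences any DLT will be allowed to continue treatment with a one dose level reduction if the toxicity resolves within 14 days". The next sentence is "If this patient experiences a DLT at the lowered dose level, study treatment will be stopped for this patient". Neither sentence distinguishes by type of event or by causal drug.
- **Section 5.2:** "Non-hematologic DLT is defined as any grade 3 or grade 4 non-hematologic toxicity that occurs during the first cycle of treatment". Severe rash, diarrhoea or pneumonitis in cycle 1 is therefore a DLT. Pneumonitis is among the toxicities singled out there for detailed recording.
- **Section 5.1, pointer:** "Appropriate dose modifications for Oral Vinorelbine and Erlotinib are described in Section 6".
- **Section 6:** after significant toxicity in cycle 1, treatment waits for recovery and the next cycle starts one level lower, by reference to a table. The table has a vinorelbine ladder (levels -1 and 1 to 5) and a separate erlotinib ladder of two levels, 100 mg and 150 mg. A further paragraph allows a drug to which a clinically significant toxicity is attributed to be stopped, with the other drug continued alone.
- **Section 2.1.2, Dose Modifications:** "If ILD is diagnosed, TARCEVA should be discontinued and appropriate treatment instituted as necessary" and "When dose reduction is necessary, the TARCEVA dose should be reduced in 50 mg decrements". For severe diarrhoea and skin reactions it says only that reduction or temporary interruption may be needed.
- **Section 2.1.2, Warnings, Pulmonary Toxicity:** "If ILD is diagnosed, TARCEVA should be discontinued and appropriate treatment instituted as needed".

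**The concern.** The continuation rule is worded for every DLT, but the dose levels it relies on move only one of the two drugs until the 150 mg cohort is reached. An investigator who follows Section 5.1 literally after an erlotinib-related DLT could lower vinorelbine and restart erlotinib at the dose on which the event occurred. For ILD, which the protocol itself describes as sometimes fatal, the same sentence permits continuing after resolution, where Section 2.1.2 says that erlotinib should be discontinued.

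At stake are the safety of individual patients and consistent handling of DLTs between patients. The primary endpoint is not directly at stake: the reduction comes after the DLT has occurred and been counted, so the documents do not show that the MTD determination is affected.

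**Working it through.** No sample-size or power figure bears on this point. The check compares the tables and text with one another.

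**1. What a one-level step changes (Sections 5.1 and 6)**

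| Step | Conventional vinorelbine (mg/m²) | Metronomic vinorelbine (mg/week) | Erlotinib (mg) | Change in erlotinib |
|---|---|---|---|---|
| 5 to 4 | 80 to 70 | 180 to 160 | 100 to 100 | 0 |
| 4 to 3 | 70 to 60 | 160 to 140 | 100 to 100 | 0 |
| 3 to 2 | 60 to 50 | 140 to 120 | 100 to 100 | 0 |
| 2 to 1 | 50 to 40 | 120 to 100 | 100 to 100 | 0 |
| 1 to -1 | 40 to 30 | 100 to 80 | 100 to 100 | 0 |

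All five steps in each schedule leave erlotinib unchanged.

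**2. Whether the erlotinib ladder fills the gap.** Section 6 lists 100 mg as its lowest erlotinib level, so a listed step down exists only from 150 mg. Section 2.1.2 describes 50 mg decrements: 150 - 50 = 100 mg is in the table, but 100 - 50 = 50 mg is not. For patients on 100 mg, the erlotinib modification that Section 5.1 says is in Section 6 is absent, apart from stopping the drug.

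**3. The 150 mg cohort.** The patient is at vinorelbine level 5 and erlotinib level 2. One level lower can mean vinorelbine level 4 with erlotinib 150 mg, vinorelbine level 5 with erlotinib 100 mg, or both. The two ladders share the numbers 1 and 2, and the text does not choose between these readings.

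**4. ILD, side by side**

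| Place | Effect after ILD |
|---|---|
| Section 5.2 | Grade 3 or 4 in cycle 1 is a DLT |
| Section 5.1 | Continuing one level lower is permitted if resolved within 14 days |
| Section 6 | The causal drug may be stopped; optional, ILD not mentioned |
| Section 2.1.2 (two places) | Erlotinib should be discontinued; no condition on resolution |

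The first two rows together permit what the last row advises against.

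**5. Whether ILD can fall within the rule.** Section 2.1.2 gives onset from 5 days to more than 9 months after starting erlotinib, with a median of 39 days. Erlotinib starts on day 3 of a 21-day cycle, so cycle 1 contains 21 - 3 + 1 = 19 days of exposure. Onset in cycle 1 is possible (5 < 19). Because the median of 39 exceeds 19, at least half of such events would be expected after cycle 1, if that distribution carries over.

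**6. Size.** Multiplying the quoted rates by the 78-patient maximum in Section 13.2 gives 78 × 5% = 3.9 patients for grade 3/4 rash (the 100 mg plus gemcitabine rate), and 78 × 0.7% = 0.5 to 78 × 2.5% = 2.0 for ILD-like events. These products do not estimate how many patients the rule affects:
- The rates are incidences over a whole trial or over all studies, with a different or no partner drug; the rash rate is reported regardless of causality. None is a cycle-1 rate.
- The rule also requires resolution within 14 days.
- The 78 includes the 150 mg cohort, which has a listed lower erlotinib level.

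**The case against.** The strongest reply is that Section 5.1 grants a permission and orders nothing. Section 6 lets the investigator stop the responsible drug and continue the other alone, Section 5.4 ends treatment for unacceptable adverse events, and Section 7.2 leaves withdrawal and therapeutic measures to the investigator. This stands against a reading that a reader might infer, namely that patients with erlotinib-type DLTs will be retreated at full erlotinib dose. The documents support only that they may be. The reply does not remove the ILD conflict: the Section 6 provision is discretionary, does not name ILD and is not cross-referenced from the continuation sentence, and Section 5.4 does not define unacceptable.

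Four further inferences go too far:

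- **That the rule also contradicts Section 2.1.2 for rash and diarrhoea.** The wording there is permissive, and the Section 6 delay until recovery is itself an interruption. For these events the defect is the unspecified drug and the missing step.
- **That vinorelbine would be cut for toxicity it did not cause.** Section 2.1.1 reports grade 3 and 4 diarrhoea with oral vinorelbine of 2.9% + 2.4% = 5.3%, and rare interstitial pneumopathy with vinorelbine. Diarrhoea and lung events cannot be assigned to erlotinib alone; rash is the clear example.
- **That a number of affected patients can be stated.** It cannot, for the reasons under the size check.
- **That only two tablet strengths are available to the trial.** Section 8.2 says "The 100 mg and 150 mg strengths are supplied as white film-coated tablets for daily oral administration", which describes those strengths without excluding others. The Description in Section 2.1.2 also lists 25 mg tablets.

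**Conclusion.** The point holds in three parts:

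- **Gap and ambiguity.** A one-level reduction changes erlotinib by 0 mg at every step from level 5 to level -1. No erlotinib level below 100 mg is listed where Section 5.1 says modifications are described. The text does not say which drug steps down, and in the 150 mg cohort this leaves more than one reading.
- **Consequence.** A patient may be retreated at an unchanged erlotinib dose after a DLT such as severe rash.
- **Contradiction.** For ILD, the Section 5.1 permission conflicts with both Section 2.1.2 statements. The optional single-agent provision softens this without resolving it.

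The conclusion rests on reading the words any DLT literally and on the dose tables as printed. The number of patients affected cannot be estimated from the documents. This should be corrected because a stated operating rule permits something the protocol's own safety text advises against; no effect on the MTD determination has been shown.

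**What to change.** The sponsor should reconcile the continuation rule and dose table in Section 5.1, and the text and table in Section 6, with the Dose Modifications and Pulmonary Toxicity text in Section 2.1.2. The reconciled text should:

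1. state unambiguously which drug a one dose level reduction refers to, including in the erlotinib 150 mg cohort;
2. remove the contradiction between the continuation permission and the Section 2.1.2 statements on ILD, and make clear how the optional single-agent provision in Section 6 relates to it;
3. make the erlotinib ladder in Section 6 and the description of decrements in Section 2.1.2 agree.

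How these are settled is the sponsor's clinical decision; no dose or clinical rule is proposed here. The cost is amendment wording in Sections 5.1 and 6. Section 8.2 needs a change only if the reconciled text calls for another tablet strength. The DLT definition and sample size need not change.
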